### Follow-up assessments

Eight and 12 months after the baseline assessment, both the experimental group and the control group are administered the Alcohol TLFB (covering the period from the previous assessment to the present), the NHS resource utilisation questionnaire, the Drinking Urges Questionnaire, the Alcohol Stroop Test, the OCDS, the POMS, the HADS, and the BDI.

### BRAINTRAIN core outcome measures

Some of the assessment instruments named above are part of the BRAINTRAIN core outcome measures, i.e. they are given in all five of the centres involved in the BRAINTRAIN project. Some of them (e.g. those measuring intellectual functioning and thought control) are used mainly to predict who will perform better at NFT and benefit more from it clinically. These measures will be used to stratify patients, and they are largely exploratory. Other instruments in this set measure nonspecific clinical factors and comorbidities (e.g. depression, anxiety) and are included across the different trials to increase the power of secondary outcome measures and to examine nonspecific effects of NFT on mental health (across different diagnoses and research protocols).

Participants are being sent reminders to attend the follow-up sessions.

Whenever possible, outcome data will be collected for all participants whether or not they adhere to the planned intervention. The data will be analysed according to the intention-to-treat principle.

### Intervention

During the baseline assessment, participants also perform a computer-based rating task, in which they are presented with a total of 100 pictures showing different categories of alcoholic beverages (wine, beer, spirits, etc.) and pub scenes and 100 pictures illustrating alternative, healthy goals (positive personal relationships, health and fitness, employment and career, further education/self-improvement, and personal finances). For each alcohol-related picture, participants are asked to indicate (by using the mouse to move the cursor along a visual analogue scale on the screen) how much this specific picture makes them want a drink of alcohol; response options range from *not at all* to *very strongly*. Using the same response modalities, participants rate each of the pictures related to an alternative goal with regard to how much it reminds them of a positive goal that they are currently pursuing. For each of the subsequent NFT sessions in which alcohol-related pictures are down-regulated or alternative goal-related pictures are up-regulated, the pictures are randomly selected from the 14 pictures in each category that the participant rated most highly. Thus, the stimulus sets are tailored to each participant’s specific drinking preferences and hierarchy of alternative goals.

The NFT involves magnetic resonance imaging (MRI) during which patients lie on a movable bed inside the bore of an MRI scanner. Before entering the MRI suite, patients undergo a detailed MRI safety screening (as described earlier), including a determination of potential safety hazards (see exclusion criteria) and the removal of all metal objects, such as keys or jewellery, from their body.

While in the scanner, participants in the experimental group are again exposed to alcohol-related stimuli, such as pictures of alcoholic drinks, and they are trained to regulate their responses in specific brain regions that are activated by the stimuli. In addition, participants are exposed to pictures showing alternative, socially desirable goals, such as family/relationships or employment. The rationale for including the two categories of stimuli is that we earlier demonstrated at a neural level that heavy drinking is associated with overvaluation of alcohol and undervaluation of alternative, socially desirable goals [14]. Moreover, consistent with motivational theory [15–17], it has been shown that problem drinkers’ success in reducing their drinking is associated with the degree to which they have other satisfying alternative goals to pursue and enjoy [16].

The size of the images that participants see corresponds to the level of activation. They are told to use any kind of mental strategy at their disposal (e.g. thinking about the negative consequences of drinking) that helps to reduce size of the image (in the case of alcohol pictures) or increase size of the image and thereby the degree of brain activation (in the case of healthy, goal-related pictures).

Experimental participants have six NFT training sessions spread across 4 months, and they are also asked to practice at home the mental strategies they used in the MRI scanner. They also (1) rate their urges to drink before, during, and after each training session, and (2) complete questionnaires and other tests to measure their alcohol consumption and other relevant aspects of their behaviour. Control participants complete the same measures that are timed to coincide with their administration to the experimental group. The primary outcome measures are obtained 4 months after the baseline assessment. Eight and 12 months after baseline assessment both groups complete a follow-up assessment battery.

For the duration of the scanning session, several additional physiological parameters are measured, including heart rate via a finger pulse sensor and respiratory rate via a belt affixed to the participant’s chest. Participants are able to see outside the scanner during the scan, and radiographers are able to see and monitor participants from the control room. Participants are given a call button to press if they need to communicate with someone outside the scanner. The scan can be stopped at any time at a participant’s request (e.g. if he or she feels uncomfortable) or if the radiographer becomes concerned about a participant’s wellbeing.

Imaging data are acquired using the 3T General Electric HDx or Siemens Prisma scanners at the Cardiff University Brain Research Imaging Centre (CUBRIC) and standard parameters for functional and structural brain imaging. Blood oxygenation level-dependent (BOLD) signals during localiser and neurofeedback runs (see description below) are measured with a T2*-weighted gradient echo planar imaging (EPI) sequence that is synchronised to the onset of the stimulus presentation. Each functional EPI volume contains 24 slices of 2.5-mm thickness, with 0.5-mm inter-slice spacing (in-plane resolution = 3 mm, matrix size = 64 × 64, FoV (field of view) = 192 mm, TR (repetition time) = 1500 ms, TE (echo time) = 30 ms, flip angle = 80°, orientation = transversal). High-resolution structural images are acquired before the first functional scan using a fast spoiled gradient echo sequence (FSPGR) with 172 contiguous sagittal slices of 1-mm thickness (voxel size: 1 × 1 × 1 mm, TR = 7.9 s, TE = 3.0 ms, flip angle = 20°, FoV = 256 × 256 × 172 mm).

The basic neurofeedback setup being used in the trial is illustrated in Fig. 2. Patients are asked to lie still throughout the scanning sessions; they are in the scanner for no longer than 90 min. During the scan, patients are exposed to pictorial stimuli (depicting either alcoholic drinks or alternative goals), which are projected onto a screen behind the scanner and viewed through a mirror attached on the MRI head coil. Functional MRI (*f*MRI) data are acquired in short blocks (*runs*) having a duration of 7.5 min. The first run serves as the localiser procedure in which we present in alternating blocks of 30-s alcohol-related pictures or goal-related pictures and neutral pictures (household objects). Each block contains 15 different pictures of the same category (2 s per picture) and is followed by a fixation (rest) period. Participants are instructed to attentively watch the pictures without any cognitive/emotional regulation of the responses that are elicited by these pictures. Based on real-time preprocessing and statistical analysis of the BOLD signal recorded during the localiser, a specific target brain area (either alcohol- or goal-related) is individually selected for each participant in each session. Statistically significant regions of interest (ROIs) are selected using a t-contrast of alcohol/goal-related versus neutral images, and a variable t-threshold to ensure that a robust cluster is activated in a functionally relevant area (minimum of four connected voxels).

**Fig. 2 Fig2:**
[figure not shown]
Illustration of the neurofeedback setup used in the intervention group. Participants receive real-time feedback about the computed activation level in target areas that have been identified in a preceding *localiser* scan as key components of the motivational network involved in alcohol-cue reactivity. Activation levels are represented as varying picture sizes, with decreasing picture sizes reflecting successful down-regulation

The next four runs consist of two NFT runs, during which the participant attempts to self-regulate activation in the target area, and two mirror (M) runs in the order NFT-M-NFT-M. During mirror runs, the previous feedback-modulated stimulus is presented, but participants are instructed to passively view it and not attempt to regulate their response. These runs serve as a control for potential low-level image size effects on activation in the target area. They will allow a comparison to be made between the same stimulus presentation with and without attempted self-regulation. Selection of both sets of pictures is based on the computer-based rating task that the participant performed during the baseline session.

Each neurofeedback run consists of seven regulation blocks of 30-s duration showing one picture exemplar whose size changes according to the participant’s BOLD activation in the target area. Between regulation blocks, a 30-s resting block showing a fixation cross is interspersed, and each run begins with a 30-s rest block. Feedback is provided by varying the size of the picture, which can range from between 100 % of the entire projector screen (1024 × 768 pixels) and 10 % of the screen, depending on the level of activation.

Down-regulation is signalled by decreasing the size of the picture, following a procedure piloted by our research group for food-related stimuli [18]. Up-regulation (during exposure to other goal-related pictures) is signalled by increases in the size of the picture. The aspect ratio of the pictures is kept constant for all picture sizes. The size of the picture is changed based on the percentage of the signal change in the current block compared to the baseline in the previously defined ROI. The last five volumes prior to the current neurofeedback block are used to calculate the baseline level.

A moving average filtre of four volumes is used to overcome spikes and signal drops and to avoid large fluctuations in the size of the pictures. The percentage signal change is calculated using this equation:$$ fb = \left( val-bl\right)/bl\ast 100 $$

The percentage signal change (PSC) is then normalised to a value between −1 and +1 by dividing the *fb* value by a predefined maximum PSC of 1 %. This is done in order to be able to resize the pictures in the predefined way.

Between the *f*MRI runs, the experimenter speaks to the participant using an intercom and gives the participant the opportunity to rest. Participants in the control group are invited to attend four behavioural assessment sessions (baseline assessment, primary assessment after 4 months, and a follow-up assessment after 8 and 12 months).

All adverse events and serious adverse events (SAEs) will be recorded on the appropriate Case Report Form. Events meeting the criteria for a SAE will be reported according to the timelines specified in the study protocol (e.g. an SAE form should be completed for all SAEs within 24 h).

Post trial, all participants will remain under the care of their primary treating physician. Cardiff University will provide indemnity and compensation in the event of a claim by a participant, or by someone on a participant’s behalf, for negligent harm as a result of the study design and/or in respect of the protocol authors/research team. Cardiff University does not provide compensation for non-negligent harm.

### Sample size estimation

There are no published randomised trials to inform a sample size calculation for the early phase efficacy trial of the neurofeedback intervention that is being evaluated. However, experimental neurofeedback studies have found large effect sizes of 0.5 to 1.5, depending on the patient group that was tested [5, 6]. At a significance level of 0.05, the present sample size (from which we expect a 20 % dropout rate, yielding a final size of 40 (or 20 in each group)) will allow us to detect effect sizes ranging from 0.8 with 70 % power to 1.1 with 90 % power. This level is suitable for single-site, early-phase detection of clinically promising results.

The behavioural data will be analysed using SPSS or another appropriate statistical software package. The primary analyses will compare the experimental and control groups on three drinking indices (percentage of days abstinent, drinks per drinking day, and percentage of days of heavy drinking) at the primary endpoint (4 months after the baseline assessment). For these analyses, a general linear model will be used. Covariates will include potential variables that determine participants’ success with the NFT (e.g. their age and gender and drinking indices at baseline) and the variables that were used to balance the two groups during randomisation. Effect sizes for the intervention will be evaluated using confidence intervals around the group difference. Analyses will be conducted separately for the follow-up assessments, again using general linear models adjusted for baseline covariates and randomisation variables. Outcome measures related to craving will be evaluated for both immediate and sustained effects of the NFT.

In exploratory analyses, data from the homework diaries will be examined for a potential relationship between the amount of self-regulation practice that participants report and their scores on craving and alcohol consumption. Finally, the relationship between nonalcohol-related measures (e.g. thought control ability, intellectual ability) and the alcohol-related outcome measures will be examined using analysis of covariance (ANCOVA) or correlational and regression analyses. Nonspecific effects of the NFT on participants’ mood will be examined using the measures related to emotional processes (e.g. the POMS).

A publication policy will be developed and reviewed during the course of the trial, which will include details of dissemination plans to health care professionals. Publications from the BRAINTRAIN consortium will be coordinated by the Executive Committee of BRAINTRAIN (chaired by the PI) in collaboration with the funding organisation. The trial results will be submitted for publication in an online open access journal.

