### Study objectives

The main aims of the Cardiff arm of BRAINTRAIN are (1) to determine whether participants who receive rtfMRI NFT can down-regulate their brain activation while they are exposed to alcohol stimuli (or up-regulate their brain activation in response to pictures related to healthy goal pursuits), and (2) to determine whether, compared to control participants, the training helps patients to reduce their urges to drink and their consumption of alcohol and to bring about other improvements in their functioning. Additionally, secondary aims of the trial are to (1) identify participant characteristics that are related to success with the training, and (2) refine the parameters of the training in order to achieve an optimal intervention.

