## Discussion

Alcohol dependence is a recalcitrant disorder, with high rates of relapse to heavy drinking occurring following treatment [19, 20]. In recent years, new medications and psychosocial interventions have been tested, but with disappointing effects on rates of relapse [19]. In view of the encouraging results obtained with rtfMRI NFT in the case of other psychiatric and behavioural disorders [4–9], its use in the treatment of alcohol dependence offers great promise.

The present study allows us to evaluate the overall effectiveness of rtfMRI NFT in reducing patients’ urges to drink and various indices of their alcohol consumption. Additionally, we will be able to evaluate participant characteristics (e.g. the ability to control thoughts, anxiety, depression, intellectual ability) that help to determine patients’ degree of success with the intervention. If positive results are obtained, more cost-effective techniques for helping patients to achieve self-control over their alcohol consumption could be developed and evaluated. Moreover, the use of these techniques could be extended to include early stage problem drinkers. Early stage problem drinkers are far more numerous in society than are dependent drinkers, yet dependent drinkers are far more costly to treat [21]. Thus, it could be highly effective and cost-effective to successfully intervene with people who are developing alcohol problems before these problems escalate into dependent drinking.

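### The analysis stated for identifying who benefits clinically from neurofeedback relates traits to outcomes without naming an arm-by-trait term, so taken literally it shows prognosis and not differential benefit

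*Protocol article*

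**What the plan says.** **The aim.** Study objectives lists as a secondary aim to "identify participant characteristics that are related to success with the training". The section on BRAINTRAIN core outcome measures says that some instruments, with intellectual functioning and thought control as examples, are "used mainly to predict who will perform better at NFT and benefit more from it clinically". It adds that they will serve to stratify patients and are mostly exploratory. The Discussion says "we will be able to evaluate participant characteristics" that help to determine how well patients do with the intervention, and names thought control, anxiety, depression and intellectual ability.

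**The analysis.** The Analyses section says that the relationship between the measures not related to alcohol (again thought control and intellectual ability) and the alcohol-related outcomes "will be examined using analysis of covariance (ANCOVA) or correlational and regression analyses". The sentence does not mention treatment group. Earlier in the same section, variables thought to determine success with NFT (age, gender and baseline drinking are the examples) enter the primary general linear model as covariates. No interaction between group and any participant characteristic is named anywhere in the article.

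**The data.** Design gives 25 randomised to NFT plus TAU and 25 to TAU alone. The Abstract says that both groups are assessed at baseline on the characteristics expected to predict success with NFT.

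**The concern.** Benefiting more from NFT is a statement about a difference: what a patient with a given trait achieves with NFT compared with what the same kind of patient achieves without it. If the trait matters, the NFT-versus-TAU difference changes with the trait. That is effect modification, and its estimate is the arm-by-trait interaction.

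A relationship between trait and outcome is a different quantity. Patients with good thought control may drink less, or crave less, whether or not they are trained in the scanner. Such a trait would show a clear association in the whole sample, and in the NFT arm alone, while saying nothing about who should be offered NFT. Conversely, a trait that helps under NFT and hinders under TAU could average to nothing in a pooled analysis. Entering supposed determinants of NFT success as covariates does not close the gap, because a covariate main effect adjusts for prognosis and does not test modification.

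At stake is a secondary aim. Prognostic traits could be reported, and carried into later trials, as markers for selecting patients for NFT.

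**Working it through.** **Inputs from the protocol article (Sample size estimation).** Significance level 0.05 (sidedness not stated; two-sided assumed). 50 randomised, "from which we expect a 20 % dropout rate", leaving 50 × 0.8 = 40, that is 20 per arm. The stated power is to "detect effect sizes ranging from 0.8 with 70 % power to 1.1 with 90 % power".

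**Step 1: reproduce the plan's figure, to fix n and sidedness.** For two means with n per arm, power ≈ Φ(d√(n/2) − 1.96).
- d = 0.8: 0.8 × √10 = 2.530, and Φ(0.570) = 71.6%. The noncentral t with 38 df gives 69.3%. The plan says 70%.
- d = 1.1: 1.1 × √10 = 3.479, and Φ(1.519) = 93.6%. The noncentral t gives 92.4%. The plan says 90%, which is conservative.

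One-sided power at d = 0.8 would be 80% to 81%, which does not fit. So 20 per arm and two-sided 0.05 are used below. These power figures concern the main group comparison only and are not disputed.

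**Step 2: a purely prognostic trait.** The article gives no trait-outcome slopes, so these are assumed. Model: outcome = b × trait + error, the same b in both arms, standard normal trait, error variance 1 − b², so that r = b. There is no differential benefit. Share of 5,000 simulated trials with p < 0.05:

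| Analysis | r = 0.3 | r = 0.5 |
|---|---|---|
| Pooled correlation (n = 40) | 48% | 92% |
| ANCOVA, trait main effect | 47% | 92% |
| Correlation in the NFT arm (n = 20) | 25% | 64% |
| Arm-by-trait interaction | 4.7% | 4.9% |

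A separate run of 6,000 trials gave 49%, 75% and 92% for the pooled correlation at r = 0.3, 0.4 and 0.5, then 25%, 42% and 64% in the NFT arm, and about 5% for the interaction.

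A hand check uses Fisher's z, power ≈ Φ(atanh(r) × √(n − 3) − 1.96).
- n = 40, r = 0.3: 0.3095 × √37 = 1.883, giving 47%.
- n = 40, r = 0.5: 0.5493 × √37 = 3.341, giving 92%.
- n = 20, r = 0.3: 0.3095 × √17 = 1.276, giving 25%.
- n = 20, r = 0.5: 0.5493 × √17 = 2.265, giving 62%.

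These agree with the simulation.

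**Step 3: a true modifier.** The slopes have opposite signs in the two arms, again by assumption.

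| Analysis | TAU −0.25, NFT +0.25 | TAU −0.4, NFT +0.4 |
|---|---|---|
| Pooled correlation | 6% | 7% |
| ANCOVA, trait main effect | 6% | 7% |
| Arm-by-trait interaction | 32% | 71% |

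**Step 4: precision of the interaction at 20 per arm.** SE ≈ σ√(1/19 + 1/19) = 0.324σ per trait SD. The 95% half-width is about 2.028 × 0.324 = 0.66σ. Simulated power is about 32% for a slope difference of 0.5 outcome SD per trait SD, 63% to 71% for 0.8, and 82% for 1.0.

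**The case against.** The case against rests largely on what the article leaves open, and much of it stands.

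- *Two of the three named methods can carry the term.* ANCOVA and regression both accept a group factor and an interaction, and checking equal slopes in a two-arm ANCOVA is itself the arm-by-trait test. The full protocol or SAP may specify it. This stands as a limit. The point is that the article states the aim as differential benefit and the analysis as a trait-outcome relationship, and the two do not match as written.
- *Which arms enter is not stated.* A reader might infer that the TAU arm is not used, or that the planned analysis cannot answer the aim. The text supports neither. It is silent on the arms, naming ANCOVA suggests a group factor, and regression with the right term would address the question.
- *The measures are also meant for stratifying patients.* One reading is a comparison of arms within trait strata, which would address differential benefit. The wording is too brief to settle this.
- *Success may mean self-regulation in the scanner.* That exists only in the NFT arm, so within-arm association is right there. The point is confined to clinical benefit.
- *The slopes are assumed, and a significant correlation for a prognostic trait is a true finding about prognosis.* Both are correct. It becomes an error only if it is read as benefit from NFT, which is the use the article states for these measures.
- *The interaction has low power.* This is true and limits what can be concluded. It does not turn a prognostic association into evidence of differential benefit.

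**Conclusion.** The point holds in a modest form. For clinical benefit, the article pairs an aim about differential benefit with a trait-outcome relationship and names no arm-by-trait term. Correlations, and ANCOVA or regression without that term, would show prognosis. If those results were read as predictors of benefit, a trait with no bearing on NFT would be flagged in about half to nine tenths of trials by the pooled correlation (48% to 92%), against about 5% for the interaction. The size rests on assumed slopes of r = 0.3 to 0.5, 20 per arm, a normally distributed trait and outcome, and two-sided 0.05. The direction of the problem does not depend on them.

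The alcohol-related outcomes include craving as well as drinking, and the reasoning is the same for both. The analysis is secondary and exploratory, and the primary group comparison is unaffected. Label: cheap improvement.

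**What to change.** - For clinical benefit, fit each alcohol-related outcome model in both randomised arms with arm, trait and arm-by-trait interaction, alongside the covariates already planned.
- Report the interaction estimate with its 95% confidence interval and mark it exploratory.
- Describe any trait-outcome association made without this comparison as prognostic only.
- Keep associations within the NFT arm for self-regulation performance in the scanner, which controls do not have.

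The cost is one model term and a sentence or two of text, on data already collected in both arms. Trial status says that recruitment is ongoing, so this can still be specified in advance. The downside is imprecision: at n = 40 the interval will span roughly ±0.66 residual SD per trait SD, so most results will inform later trials and not settle who benefits.
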